| Behavioural Target                                                                  | 
 
Knowledge and skills to deliver person-centred care
 
Increased salience, motivation, and identification of opportunities to deliver more person-centred care
 
Increased of PCC behaviors, including being more welcoming, empathy, improved communication, shared decision making, and leveraging discretionary power to better accommodate client needs.
 
 |
| Temporality                                                                         | 
 
Training HCW on PCC at 0m for Group 1, 7m for Group 2, 13m for group 3 and 19m for Group 4
 
Mentorship begins immediately after first batch of HCWs trained in PCC
 
Synthesis meeting 6 weeks after training
 
Client experience data review meetings every 3 months
 
Incentive for best performing facility every 6 months
 
                |
| Dose                                                                                | 
 
PCC training done once for two days for each HCW
 
Weekly mentorship visits to facility till study end
 
                                                                                                                                                                                                                                                             |

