Footnote: We conducted a sensitivity analysis for the effect of the PCC intervention on missed visits that leveraged existing EHR data to include an additional Period 0 in the analysis. This Period 0 included visits made in the 6 months prior to study initiation when all facilities were in the control condition (i.e., visits made between February 12, 2019 and August 11, 2019). This approach allowed for Group 1 clinics to also have a baseline control period prior to intervention implementation included in the analysis, thereby improving statistical efficiency and power. We initially indicated this as the primary approach for assessing missed visits in the statistical analysis plan. However, as results remain unchanged, we opted to include this analysis in the supplemental appendix to allow for consistency in study and analysis designs between different cohorts in the main manuscript.

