### Study design:

We used a stepped wedge cluster randomised trial to assess the effect of the PCC intervention in 24 clinics. We introduced the intervention at four randomly-determined time points at study start, 6, 12 and 18 months. We followed all sites for a total of 24 months. The size of each sequence was not the same, with eight facilities in sequence 1, four in sequence 2, four in sequence 3 and eight in sequence four. The unequal weights allow us to power outcomes such as viral load that occur over periods of time that are longer than each period, and for which cross over would preclude comparison of each treatment condition.

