## 5.0 – Secondary Outcome – Retention in Care

### 5.1 – In Care at 15 months

**Outcome:** This secondary outcome for retention is being in care at 15 months which will be defined as not being more than 30 days late to a visit at 15 months. We will use EHR data (i.e., SmartCare) that includes sociodemographic, clinical, visit history, and pharmacy data to determine this outcome.

**Population:** The population for this outcome will include all individuals ( $\geq 18$  years old) who made a visit to one of the Wave 1 or Wave 4 study facilities in the first 6 months of the 24-month study period (i.e., period 1). We restrict to facilities in wave 1 and 4 in order to allow a minimum of 15 months of exposure to either the intervention or control conditions at the time out outcome assessment without crossover. This allows us to analyze this aim like a parallel cluster-randomized trial.

|                   | Period 1                                                                                   | Period 2 | Period 3                     | Period 4 | Totals per wave |
|-------------------|--------------------------------------------------------------------------------------------|----------|------------------------------|----------|-----------------|
| Wave 1            | Intervention
All individuals making visit to Facility during Period 1
~40,000 |          | Outcome Ascertainment |          | ~40,000         |
| Wave 2            |                                                                                            |          |                              |          |                 |
| Wave 3            |                                                                                            |          |                              |          |                 |
| Wave 4            | Control
All individuals making visit to Facility during Period 1
~40,000      |          | Outcome Ascertainment |          | ~40,000         |
| Totals per period | ~80,000                                                                                    |          |                              |          | ~80,000         |

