**Analysis:** Time zero will be the first visit a participant makes at a study facility during Period 1. Individuals will be considered to be in care if they are not more than 30 days late at the 15-month time point. We will use mixed effects logistic regression, accounting for clustering at the facility-level using random effects. The main exposure will be exposure to the PCC intervention. To account for potential imbalances due to cluster randomization at baseline and also increase precision, we will adjust for individuals' care status at enrollment (in care, new ART, LTFU), sex, age, time in care, baseline clinic-level retention (i.e., percent of visits where patient was more than 30 days late to their next appointment assessed in the 6 months prior to study start), and randomization strata (initial cluster randomization stratified by facility size and viral load coverage based on programmatic data). Facility will be included as a random effect. We will consider including the following potential

confounders due to imbalance in randomization: WHO severity groups, marital status, and education. We will use standard model diagnostic procedures and consider alternate specifications as needed if we face challenges with standard statistical issues such as model convergence or overfitting. We will use marginal estimation commands to report absolute and relative risk differences under treatment versus control conditions.

In addition to the overall analysis, we will perform stratified analyses to assess changes specifically across:

- Care Status (in care, new ART, LTFU)
- Sex
- Age (<25, 25-44, >45)
- Advanced HIV Disease at enrollment in care (WHO Stage 3 or 4, CD4<200) – Dependent on adequate coverage of CD4 measurements
- Clinic Size and Type
- We may assess composite subgroups of age, sex, and care status (e.g., Male <25 years old, LTFU not suppressed at baseline) if amenable based on sample sizes. We will not perform analyses with less than 500 participants.

**Sensitivity Analysis:** We will perform several sensitivity analyses to ensure the robustness of our results by exploring an alternative definition of 90 days late at the 15-month time point.

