## **6.0 INTERVENTION DESIGN**

The PCC intervention is a health systems intervention that seeks to improve the patient-centredness of HIV care to improve the patient experience and, ultimately, clinical and care outcomes by: 1) systematically assessing the patient experience (e.g., satisfaction, barriers to care), facility approaches to patient care (e.g., use of differentiated service delivery models, monitoring viral load, how late and lost patients are welcomed back to care), and key patient outcomes (e.g., retention); 2) providing HCWs training in patient-centred principles and skills and mentoring to improve patient-centred practice using the collected data to target action; and 3) offering incentives to motivate facilities above and beyond their innate desire to help improve patient lives.

Part 1 of the intervention is to add continuous measurement of the patient experience and outcomes using four new modalities (exit interviews, QIPS, SMS surveys, and structured assessments among patients who are lost to follow-up) along with existing data to be drawn from SmartCare and other routine data sources to highlight current standard measures of performance (e.g., retention, completeness of viral load monitoring, and possibly viral suppression and mortality). Other standard measures will include any above-facility events or trends that could influence the implementation of the PCC interventions or it’s effects on service delivery or patient outcomes. Such events include facility drug supplies and staffing levels that could affect service delivery as well as unanticipated events such as political instability or severe climate events as well as policy changes. These measurements may provide context for the observed effects.

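### SAP 5.1 forms the 15-month retention cohort from visits made after Wave 1 began the intervention, so entry and care status at entry may depend on arm, and no planned analysis tests this

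*Combined protocol and SAP*

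**What the plan says.** SAP 5.1 takes adults who "made a visit to one of the Wave 1 or Wave 4 study facilities in the first 6 months of the 24-month study period". Its table gives, for each of the two waves, "All individuals making visit to Facility during Period 1 ~40,000". The clock is individual: "Time zero will be the first visit a participant makes at a study facility during Period 1". Being in care is "defined as not being more than 30 days late to a visit at 15 months".

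The SAP's study design paragraph says "We introduced the intervention at four randomly-determined time points at study start, 6, 12 and 18 months". The intervention specification table in the appendix agrees on Wave 1 and gives "Training HCW on PCC at 0m for Group 1, 7m for Group 2, 13m for group 3 and 19m for Group 4". Wave 1 is therefore under the intervention for all of Period 1, and Wave 4 is under control.

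The model adjusts for care status at enrolment (in care, new ART, LTFU), sex, age, time in care, clinic-level retention in the six months before study start, and randomisation strata. Care status also defines a subgroup analysis. The only sensitivity analysis in 5.1 is a 90-day lateness threshold.

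Protocol 6.0 lists "how late and lost patients are welcomed back to care" among the facility practices the intervention will assess. For missed visits (SAP 5.2) the plan brings in pre-study EHR data, and the footnote to Table S13 explains: "This Period 0 included visits made in the 6 months prior to study initiation when all facilities were in the control condition". SAP 5.1 uses those six months only for the clinic-level retention covariate, not to define the cohort.

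**The concern.** SAP 5.1 says that restricting to Waves 1 and 4 allows analysis as a parallel cluster-randomised trial. That holds if arm does not affect who enters. Here entry is a visit made after randomisation and, in Wave 1, after exposure began.

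The documents give a plausible route for an effect on entry. Protocol 4.2 reports that disengaged patients, asked what would have to change for them to come back, most often named clinic-based problems such as rude staff. The appendix lists more welcoming staff behaviour as a behavioural target. Protocol 8.6.2 plans to measure the intervention's effect on the experience of lost patients who return.

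Two patients show the consequence:

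- One is lost before study start and would return only to an improved facility. In Wave 1 this patient enters as a returner. In Wave 4 the same patient never enters.
- The other is in care just before study start and never attends again. This patient is in neither arm's denominator.

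The Wave 1 and Wave 4 cohorts may thus differ because of the intervention, and bringing back patients already lost cannot count in its favour. Care status is recorded at the same Period 1 visit, so the returner stratum is itself formed after exposure.

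**Working it through.** SAP 5.1 states no sample size or power figure, so there is no plan figure to reproduce. The steps below only illustrate possible size.

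**Inputs from the documents**
- Control retention (Table S9): in care 93.9%, new ART 70.3%, returners 72.9%. These come from the traced sub-cohort (Cohort 4) and stand in for the EHR cohort.
- Reported retention effects (Table S8): overall 5.9 points (0.6 to 11.2); returners 5.0 (0.0 to 10.1).
- Returner visits (Table S13): 149,608 in all. The two intervention columns imply 8,526/0.296 = 28,804 and 14,660/0.290 = 50,552. Control is then 149,608 − 28,804 − 50,552 = 70,252, and 70,252/587,479 = 12.0%.

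**Assumed inputs**
- Extra returners in Wave 1, relative to those who would have come anyway: r = 10%, 25%, 50%.
- Retention among those extra returners: m = 40%, 50%, 60%.
- No effect of the intervention on anyone else.

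**1. Fall in Wave 1 returner retention** = r/(1+r) × (72.9 − m)

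| r | m = 60 | m = 50 | m = 40 |
|---|---|---|---|
| 10% | 1.2 | 2.1 | 3.0 |
| 25% | 2.6 | 4.6 | 6.6 |
| 50% | 4.3 | 7.6 | 11.0 |

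If m = 72.9 the fall is zero. If m is higher, the sign reverses.

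**2. Carried to the whole cohort, returner share held at 12%**
- Smallest: 0.12 × 1.17 = 0.14 points.
- Largest: 0.12 × 10.97 = 1.32 points.

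This product holds the care mix fixed, so it leaves out the change in mix.

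**3. One case followed through (r = 25%, m = 50%)**
- Assumed mix: 83% in care, 5% new ART, 12% returners. Base retention = 0.83 × 93.9 + 0.05 × 70.3 + 0.12 × 72.9 = 90.2%.
- Extra entrants are 0.25 × 12% = 3% of the base cohort.
- Crude difference: (0.902 + 0.03 × 0.50)/1.03 − 0.902 = −1.2 points.
- After perfect care-status adjustment: −4.58 × pooled returner weight (0.24 + 0.03)/(2 + 0.03) = −4.58 × 0.133 = −0.6 points. With m = 72.9 this is 0.
- On a roster that also contains these patients in both arms, counting them as not in care under control: 0.03 × 0.50/1.03 = +1.5 points.

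In this case adjustment about halves the crude bias, but it cannot restore the credit for return.

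**4. Is month 15 from a common start usable?** Wave 4 crosses over at month 18 (SAP study design), has training at month 19 (appendix), or crosses over at 6 + 9 + 6 = month 21 (Figure S1). Month 15 precedes all three.

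**The case against.** Much of the case on the other side stands.

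- The outcome is status at one time point. Someone who lapses after time zero and is back by month 15 counts as in care. A reader might infer that every effect on re-engagement is lost, but only the return of patients already lost at study start goes uncredited.
- Care-status adjustment works against the bias and removes the part counted against the intervention if extra returners resemble other returners. Pre-study clinic retention is a genuine pre-exposure covariate.
- The phrase in Protocol 6.0 describes a practice to be assessed. No protocol objective names re-engagement as an outcome, and tracing of lost patients is described as standard of care. The route is plausible, not demonstrated.
- A large inflow within six months has little support. The SAP expects a lag, with first data feedback at three months. Early effects among returners are close to null: missed visits −0.6 (−1.6 to 0.4) in Table S8, bad experience −2.2 (−13.8 to 9.3) in Table S4. These are not entry counts, but they give no reason to expect the upper end of the range.
- The protocol chose an open cohort of people with encounters. A fixed roster answers a somewhat different question.

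Two tables may tempt a reader to claim proof that composition changed. In Table S13 the returner share of visits rises from about 12.0% under control to 16.1% (28,804/178,523) and 20.8% (50,552/243,350) under intervention. That comparison is confounded with calendar time and COVID-19. In Table S9 the arms hold different numbers of returners, but that sub-cohort was recruited to a quota of a quarter lost or late, so the counts do not show who came to clinic.

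What remains is that entry and care status are set after exposure began, and nothing planned in SAP 5.1 tests whether that matters.

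**Conclusion.** The point holds as a gap in the retention analysis. The size of the bias is unknown, because the documents give no Period 1 entry counts by care status for this cohort. Under the assumed inputs, Wave 1 returner retention falls by 1.2 to 11.0 points through selection alone. The reported returner effect of 5.0 lies inside that range, so that subgroup result needs the most caution. The overall shift of about 0.1 to 1.3 points is small beside the reported 5.9. These figures rest on an assumed inflow, assumed retention among the extra returners, control retention borrowed from another cohort, and a 12% share counted in visits rather than people.

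A reader might infer that the overall benefit is an artefact. The documents do not support that: if extra returners are retained less well than others, the bias runs against the intervention. The opposite direction is possible if they are retained better, so the result cannot simply be called conservative.

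**What to change.** 1. Report Period 1 entry counts by care status and wave. This is the direct check on whether composition differed.
2. Add to SAP 5.1 a sensitivity analysis, labelled post hoc because results are already reported, on a roster fixed before the intervention:
   - Include all adults at Wave 1 and Wave 4 facilities with an EHR record before study start.
   - Use Period 0 (12 February to 11 August 2019) and extend the look-back as far as the EHR allows. A roster limited to Period 0 visits would miss patients lost before February 2019.
   - Exclude deaths and transfers recorded before study start.
   - Fix care status at study start, start the clock there for everyone, and assess status at month 15, before Wave 4 crosses over.
3. Keep the Period 1 cohort as the main analysis and for new ART starters. Read its in-care and returner subgroup results alongside the fixed-roster results; do not replace them.

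The cost is SAP wording and one further run. Period 0 data were already extracted for Table S13, while a longer look-back may need a further extract. There are two downsides to state: new ART starters fall outside the roster, and unrecorded deaths or transfers before study start add noise.

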With first diagnosed case of COVID-19 in Zambia on the 18th of March 2020, the context of the implementation of the PCC intervention has changed dramatically. As the COVID-19 pandemic progresses globally and in Zambia, the situation in which HIV care is delivered will be dynamic. Initial responses included the Ministry of Health issuing a directive on 24th March 2020 to dispense a 6-month antiretroviral therapy (ART) supply to all patients on HIV treatment, and all sites began a process of calling patients into the clinic, regardless of the timing of their last visit. In accordance with guidance from CDC and PEPFAR, community-based activities such as testing campaigns have been suspended; and resources redirected to surveillance and testing for COVID-19. Health facilities have implemented measures including screening of patients of symptoms upon arrival, triage of suspected COVID-19-positive patients, maintaining a distance of 1 metre or more between patients who are waiting to be attended to and installing additional handwashing stations. Just as the context has changed, the experience of patients and providers has changed. To understand HIV care delivery – critical and life-saving services that must continue under any circumstances – we will assess the patient and provider experiences under these conditions, leveraging the study platforms established for prior measurements.

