#### 8.7.1.2 Full cohort-for retention in care

We will, nevertheless, also assess endpoints on the entire clinic based cohort represented in the EMR, using outcomes that can be assessed in the electronic medical record, specifically retention using visits, transfer and passively collected vital status. Since all patients who experience an encounter during the 24-month study period will be examined for the retention endpoint, which we anticipate based on current program data to be-as many as 170,000. We seek a waiver of consent for measurement of clinical care and outcome data in this

cohort. Reviewing patient outcomes as recorded in routine medical records is of minimal risk. It is not possible to seek written consent from the entire cohort of patients. We will treat known deaths as lapses in treatment.

Figure 1

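### SAP 5.1 defines 15-month retention by lateness alone and omits the protocol's rule on known deaths, so a recorded death can be scored as in care

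*Combined protocol and SAP*

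**What the plan says.** SAP 5.1 (Outcome) describes the endpoint as "being in care at 15 months which will be defined as not being more than 30 days late to a visit at 15 months". Its Analysis paragraph repeats the test: "Individuals will be considered to be in care if they are not more than 30 days late at the 15-month time point". On data it says "We will use EHR data (i.e., SmartCare) that includes sociodemographic, clinical, visit history, and pharmacy data to determine this outcome"; vital status is not named. The one sensitivity analysis is "exploring an alternative definition of 90 days late at the 15-month time point".

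Protocol 8.7.1.2 covers the full EMR cohort for retention. It lists the outcomes to be assessed as "specifically retention using visits, transfer and passively collected vital status" and adds: "We will treat known deaths as lapses in treatment". Protocol 8.8 would also explore competing risks for mortality if deaths are not trivial in number.

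The SAP neither repeats nor withdraws these provisions. For its primary outcome (SAP 2.1) it does name death as a component of treatment failure.

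**The concern.** A lateness test cannot see a death until the next appointment has been overdue for long enough. Suppose a patient is seen at month 10 with the next visit due at month 16, and dies at month 12. At month 15 that patient is not late, so SAP 5.1 as written scores in care even if the death is in the record. Protocol 8.7.1.2 would score a lapse.

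The window matters more in this trial than it would usually. Period 1 ran from August 2019 until Period 2 began in February 2020, so the 15-month points fall between about November 2020 and May 2021. The March 2020 directive to "dispense a 6-month antiretroviral therapy (ART) supply to all patients on HIV treatment" precedes all of them. The note to Figure S6 says that appointment intervals lengthened greatly during the pandemic and gives this as a reason for changing the missed-visit analysis. The longer the interval, the longer a death stays undetected by a lateness test.

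At stake is whether the worst outcome can be counted as a success in a named secondary endpoint whose reported lower confidence limit is 0.6 points. Moving from 30 to 90 days enlarges the misclassification, so the planned robustness check cannot reveal it.

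**Working it through.** **Inputs from the documents**

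- Deaths, Table S11 (Cohort 4): 4/453 control, 10/480 intervention, p = 0.132.
- Retention risk difference, Table S8 (overall): 5.9 points (0.6 to 11.2).

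**Reproducing the plan's figure.** 4/453 = 0.88% and 10/480 = 2.08%, a difference of 1.20 points. The Pearson chi-square without continuity correction gives p = 0.1317, which matches 0.132.

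**Assumptions not in the documents**

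- Appointments are L months apart, with L = 3 or 6. Six is prompted by the dispensing directive.
- At death, the time to the next appointment is uniform on 0 to L.
- Deaths over the 15 months are either uniform or front-loaded, with death time = 15 × Beta(1, 1.5).
- The grace period g is 1 month (30-day rule) or 3 months (90-day rule).
- Table S11 death rates stand in for the full cohort.

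**Share of deaths scored in care.** A death at time d with r months left to the next appointment is not yet late at month 15 if d + r + g ≥ 15.

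- Uniform deaths: share = (L/2 + g)/15. For L = 6 and g = 1 this is (3 + 1)/15 = 0.267.
- Front-loaded deaths: share = [(L + g)^2.5 − g^2.5] / (2.5 × L × 15^1.5). For L = 6 and g = 1 this is (129.6 − 1)/(15 × 58.09) = 0.148.

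**Shift in the risk difference** = share × 1.20 points.

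| Deaths | L (months) | 30-day share | 30-day shift | 90-day share | 90-day shift |
|---|---|---|---|---|---|
| Uniform | 6 | 27% | 0.32 | 40% | 0.48 |
| Uniform | 3 | 17% | 0.20 | 30% | 0.36 |
| Front-loaded | 6 | 15% | 0.18 | 26% | 0.31 |
| Front-loaded | 3 | 7% | 0.09 | 17% | 0.20 |

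**Against the reported result (30-day rule).** As an approximation, subtract the shift from the adjusted estimate and from its lower limit. The estimate becomes 5.9 − 0.32 = 5.58 at one end and 5.9 − 0.09 = 5.81 at the other. The lower limit becomes 0.28 to 0.51.

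**Extreme bound.** If every death were scored in care, the shift would be the full 1.20 points, giving an estimate of 4.7 and a lower limit of −0.6. This is not realistic: a patient who dies early in follow-up would be more than 30 days late well before month 15 at any interval considered here.

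**The case against.** The strongest reply is that SAP 5.1 is silent on death and does not order that deaths count as in care. Protocol 8.7.1.2 was not withdrawn, so an analyst reading both documents could already treat recorded deaths as lapses. That is fair as to what was done: the documents do not show how deaths were handled. It does not remove the conflict. The SAP is the later document, it states a complete classification rule, and that rule gives a different answer from the protocol's for the same patient.

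A reader might infer three stronger things, none of which the documents support.

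- *That the reported 5.9 points counts deaths as successes.* Nothing shows how the EHR deaths were coded.
- *That the error favours the intervention.* This rests on 4 against 10 deaths. The crude difference of 1.2 points has an approximate 95% interval of −0.3 to 2.7, before any allowance for clustering.
- *That the number of patients affected follows from multiplying Table S11 rates by about 40,000 per arm.* Those deaths come from a sub-cohort that was sampled as one quarter new on ART and one quarter lost or late, and was intensively traced where no viral load existed. The full cohort has passively collected vital status, and only recorded deaths are in dispute, because unrecorded deaths are scored by lateness under either document. The number of recorded deaths is not given.

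The 6-month interval can also be questioned. The directive is described as an initial response, and the SAP planning figures for Wave 1 (about 40,000 people in 5.1, about 60,000 visits per period in 5.2) imply 1.5 visits per six months, or about 4 months apart. That lies inside the 3-to-6-month range used above.

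**Conclusion.** The point holds as a conflict between the two documents that needs to be settled in the SAP. SAP 5.1 omits the protocol's provision for known deaths and, applied literally, scores some recorded deaths as in care.

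The likely size is small: about 0.1 to 0.3 points on the reported difference under the 30-day rule, and 0.2 to 0.5 under the 90-day rule. These figures assume intervals of 3 to 6 months, uniform or moderately front-loaded deaths, and that the Cohort 4 death rates carry over. The shift from recorded deaths alone is probably smaller, and its direction is uncertain. In every case other than the extreme bound the lower limit stays above zero, so the retention conclusion is unlikely to change. The reason to act is that the endpoint should mean what the protocol says it means, and that readers need to know how deaths were counted.

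**What to change.** Add to SAP 5.1:

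> In care = not known to have died on or before the 15-month time point and not more than 30 days late at that point; a death recorded in the EHR on or before that date is not in care, whatever the next appointment date.

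Apply the same clause to the 90-day sensitivity analysis. Re-run the retention model, and report by arm the number of recorded deaths and the number reclassified. If the analysis already handled deaths this way, saying so and giving the counts is enough.

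The cost is one sentence and one recode from vital status that the protocol already lists. Two limits remain. Deaths not recorded in the EHR are still scored by lateness. Recording may also differ between sites or arms, which is why the counts by arm should accompany the estimate. For the same reason the clause is confined to deaths in the EHR: the documents describe routine facility tracing for this population, not systematic ascertainment across the cohort.
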